#### Secondary outcome measures

2.4.2

We will use the National Institutes of Health Stroke Scale (NISHH) before and after treatment to assess patients’ daily living ability, including eating, transferring, grooming, bathing, toileting, walking, dressing, going down stairs, and urination control. Out of 100 points, the higher the score and the stronger the living ability. Observe the clinical efficacy, the judgment criteria are as follows: obvious effect: nausea, drowsiness, limb numbness, and other symptoms disappear, ADL score increased by more than 75%; improvement: clinical symptoms reduced, ADL score increased by 25% to 75%; invalid: clinical symptoms did not improve significantly The ADL score improved by <25%.

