#### Inclusion criteria

2.2.2

This study will be conducted in China. Patients will be recruited from urology/neurology departments of Dongzhimen Hospital Affiliated to Beijing University of Chinese Medicine. We will enroll participants based on the following inclusion criteria:

1.Those who meet the western medical diagnostic criteria for impotence (ED) and occur after stroke;2.20 ≤ age ≤ 60 years old male, normal sexual desire;3.The vital signs are stable and the stroke recovers;4.All are first stroke.5.Accept and sign the informed consent

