The factors that affect the sexual function of stroke patients are many and complex. Stroke location, area, disease occurrence and development process may affect patients’ sexual function. Therefore, this study made strict rules on case selection, excluding patients who could not take care of themselves and had emotional cognition disorders; when selecting cases, patients had a recent stroke >3 months to ensure that the stroke was stable and chose to comply as much as possible Patients with better sexuality and cooperation should conduct a questionnaire study to reduce the impact of other factors on the patient's sexual function.^[16]^ The manifestation of sexual dysfunction in young and middle-aged male patients is mainly ED. In sexual activity, men are often active acquirers, and the occurrence of ED is determined by multiple factors. Studies have shown that the high-risk factors that affect men's erections are mainly related to patients’ smoking history, high blood pressure, worries about recurrence of stroke, and daily antihypertensive receptor inhibitors. The possible reasons are:

1.the influence of subjective assessment of husband and wife relationship. Due to privacy and the personality of Chinese people, most respondents are unwilling to proactively expose their rapport with their spouse, affecting the final statistics.2.Most studies have shown that emotional instability in patients can affect sexual quality of life.

After excluding those cases with depression and anxiety, they found that abnormal changes in mood can significantly affect the quality of sexual life of patients.^[17]^ Further interviews with patients showed that some patients had misunderstandings and even fears about normal sexual life, and worried that intense sexual life would increase the risk of stroke. This misunderstanding is completely unnecessary, which further confirms the lack of clinical related guidance and deserves further attention in the clinic. Therefore, we will evaluate the clinical effectiveness and safety of acupuncture in the treatment of PSED. We hope that the results of this study will provide clinicians with the basis for acupuncture treatment of PSED and more treatment options.

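### The only secondary outcome names a stroke scale but scores a 100-point daily-living scale, and its percentage grades cannot all be reached and do not cover every patient

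*Protocol article*

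**What the plan says.** All of the outcome definition is in section 2.4.2 of the protocol article, Secondary outcome measures.

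- **Instrument:** "We will use the National Institutes of Health Stroke Scale (NISHH) before and after treatment".
- **Content:** the scale is said to assess daily living ability, "including eating, transferring, grooming, bathing, toileting, walking, dressing, going down stairs, and urination control".
- **Range and direction:** "Out of 100 points, the higher the score and the stronger the living ability".
- **Top grade (obvious effect):** listed symptoms gone, and "ADL score increased by more than 75" per cent.
- **Middle grade (improvement):** symptoms reduced, and "ADL score increased by 25% to 75" per cent.
- **Lowest grade (invalid):** no significant symptom improvement, and "The ADL score improved by <25" per cent.

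The term ADL appears only in this section. No instrument is attached to it, and the denominator of the percentages is not stated.

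On the population, Inclusion criteria (2.2.2) require that "The vital signs are stable and the stroke recovers". The Discussion describes case selection as "excluding patients who could not take care of themselves", with the stroke more than 3 months earlier.

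**The concern.** The section gives two incompatible accounts of one measurement. The name points to a stroke scale. The items, the 100-point total, the direction and the response rule all point to a daily-living scale. Someone preparing the case report form could follow either, and a form that was never administered cannot be recovered at analysis.

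Even with the daily-living reading settled, the response rule is awkward. Percentage gains on a scale that stops at 100 become harder to achieve, and then impossible, as the starting score rises. The descriptions of recovery and self-care suggest that some patients will start high. For them the grade would be limited by the baseline score, whatever the treatment does.

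**Working it through.** The plan gives no sample size, power or expected value for this outcome, so there is no stated figure to reproduce.

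**Step 1: name against description.** The listed items are daily activities, the section calls what is assessed living ability, the total is 100, higher is better, and the graded quantity is an ADL score. None of these is tied to the named stroke scale except by the opening sentence. Four features agree with each other and disagree with the name.

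**Step 2: ceiling if the percentage is relative to baseline.** Inputs are the maximum of 100 and the cut-offs of 25% and 75%, all from section 2.4.2. A patient with baseline b can gain a fraction c only if b(1 + c) ≤ 100, that is b ≤ 100/(1 + c).

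- c = 0.25: b ≤ 100/1.25 = 80. Above 80 a 25% gain is impossible. At exactly 80 it requires a perfect final score.
- c = 0.75: 100/1.75 = 57.1. Above this a gain of more than 75% is impossible.

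The largest possible gain is (100 − b)/b. Examples are 66.7% at b = 60, 42.9% at 70, 25.0% at 80, 17.6% at 85 and 11.1% at 90.

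**Step 3: other readings of the percentage.**

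- Points on the 100-point scale: a gain of 25 needs b ≤ 100 − 25 = 75, and a gain above 75 needs b < 100 − 75 = 25. A ceiling remains.
- Share of possible gain, (after − b)/(100 − b): every cut-off can be reached for any b below 100. There is no ceiling.

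**Step 4: how many patients.** No baseline ADL scores are given. The table shows the share blocked under assumed baselines: normal weights on a 0 to 100 grid in steps of 5, with SD 10, 15 and 20, and the percentage relative to baseline. Each entry is the range over the three SDs.

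| Assumed mean | Cannot exceed 75% | Cannot reach 25% |
|---|---|---|
| 50 | 22–35% | 0–5% |
| 60 | 54–60% | 1–12% |
| 70 | 72–90% | 10–23% |
| 80 | 85–99% | 37–39% |
| 85 | 90–100% | 44–58% |
| 90 | 93–100% | 52–75% |

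Under these assumptions a majority misses the top grade once the mean is about 60. A majority misses both response grades only at a mean of about 85 to 90.

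**Step 5: do the grades cover everyone?** Take a patient who starts at 90 and whose symptoms disappear. His gain is at most 11.1%, so he fails the ADL part of the top and middle grades. His symptoms have improved, so he fails the symptom part of the lowest grade. He has no grade. This reads both parts of each grade as required. The same gap catches any patient whose symptoms improve while the ADL gain stays under 25%. A patient starting above 80 whose symptoms improve cannot avoid it.

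**The case against.** The strongest reply is that the name is a slip. The section itself fixes the items, the total, the direction and the graded score, so a sensible reader would administer a daily-living scale. That is plausible, and it answers one tempting inference: that the trial will score a deficit scale backwards and call worsening a response. The only direction the section states is that higher is better, and the article gives no range or direction for the stroke scale. The inference would apply only if the named scale were in fact used. The contradiction remains and has to be reconciled.

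A reader might also infer that most patients in this trial cannot respond. The document does not support that. It gives no baseline scores, and the evidence on impairment is mixed. Inpatients are eligible (Participants, 2.2). Rehabilitation in the intervention group begins with passive activities and turns active only when muscle strength reaches level 3 (Interventions, 2.3). The self-care restriction appears in the Discussion but not in the Exclusion criteria (2.2.3).

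Nor are high-baseline patients always graded invalid, because that grade also requires that symptoms did not improve significantly.

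Two further points stand in part. The ceiling depends on a denominator that the text leaves open, and one reading removes it. Also, Statistical analysis (2.7) already provides t, rank-sum and repeated-measures methods for measurement data, so the score need not be analysed only through the grades. But section 2.4.2 gives the grades as the efficacy criteria, and 2.7 does not say how this outcome will be compared.

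**Conclusion.** The point holds as an error of definition. Section 2.4.2 contradicts itself about its instrument, and this conclusion needs no assumption about patients.

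The ceiling is conditional. If the percentages are relative to baseline, the limits are 57.1 for the top grade and 80 for the middle grade. The number of patients affected is unknown; the shares tabulated above rest on assumed baseline distributions. The gap between the grades follows from reading the symptom and ADL conditions as jointly required.

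The consequence is confined to the secondary outcome. The primary outcome and the sample size rest on IIEF-5 and are not touched. The definition should nevertheless be settled before recruitment, because the wrong form cannot be corrected afterwards.

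**What to change.** 1. Name the 100-point ADL index as the instrument for the items and scoring described. If the stroke scale is also wanted, list it as a separate outcome with its own range and direction.
2. Replace the 25%/75% grades with a between-group comparison of the after-treatment ADL score, adjusted for the baseline score. This removes the unreachable cut-offs and the gap between grades. It does not remove the upper limit of the scale itself, so the baseline distribution should be reported by group.
3. If the grades are kept, state the denominator of the percentage and define the grades so that every combination of symptom change and ADL change falls into exactly one.

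The cost is wording in the protocol and case report form, with no extra visits for the ADL measure. The article says that recruitment has not started and that the plan is still to go to the ethics committee, so the change can be made now. The small downside is that the result is no longer reported in the familiar response grades.

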### Interventions

2.3

Control group: The control group will be given conventional treatment to regulate blood pressure, blood glucose, and blood lipid. At the same time, drugs such as nutritional nerves, promoting blood circulation, and removing blood stasis are used, adjusted according to the needs of the disease, and routine rehabilitation training is performed.

Intervention group: This group of patients will be given acupuncture combined with rehabilitation training. TCM acupuncture therapy: Acupoints include *Quchi*, *Waiguan*, *Hegu*, *Dicang*, *Sanyinjiao*, and *Zusanli*. The twisting technique will be used, leaving the needles for 30 min, and treated once a day for 2 weeks. Rehabilitation training is first of all passive activities. With the help of ropes, sticks and other tools, fists, leg lifts, cross fingers, etc are performed 3 times a day for 30 min each time. When the muscle strength returns to level 3, take active training, including voluntary turning, sitting exercises, standing exercises, walking training, etc. The total application time will be 8 weeks. At the same time, closely monitor the change of the condition in order to control the deterioration of the condition in time.

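### The secondary efficacy grades tie a symptom result to an ADL-gain band with no rule for disagreement, so six of nine combinations have no unique grade

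*Protocol article*

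**What the plan says.** Section 2.4.2 (Secondary outcome measures) describes a daily-living score taken before and after treatment: "Out of 100 points, the higher the score and the stronger the living ability". It then sets three efficacy grades, each with a symptom part and an ADL part (all figures are percentages):

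- Top grade: "obvious effect: nausea, drowsiness, limb numbness, and other symptoms disappear, ADL score increased by more than 75".
- Middle grade: "improvement: clinical symptoms reduced, ADL score increased by 25% to 75".
- Bottom grade: "invalid: clinical symptoms did not improve significantly The ADL score improved by <25".

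The two parts are joined by a comma in the first two grades and by nothing in the third. The section has no rule for a patient whose symptom result and ADL band point to different grades, and none for a patient who has no symptoms at baseline.

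**The concern.** A grading rule should give each patient exactly one grade. The primary grades in section 2.4.1 come close to this: they rest on one score, the IIEF-5, and cover its range. The secondary grades add a second condition and lose that property. A man whose numbness disappears with a 10% ADL gain, or whose ADL score rises 40% with unchanged symptoms, has no clear place.

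The evaluator would have to place such men by judgement, or the analyst would have to leave them out. The graded rate would then depend on an unstated convention or on a selected subset, and a second team could not reproduce it from the protocol. There is a further difficulty. Symptoms cannot disappear or lessen in a man who never had them, so the symptom clause can block a favourable grade on what is meant to be a measure of function.

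**Working it through.** The plan states no sample size, power or rate for this outcome, so there is no figure to reproduce. The check lists every combination and counts the grades it receives.

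**Inputs, all from section 2.4.2.** Symptom result: disappeared, reduced, or not significantly improved. ADL gain: above 75%, 25% to 75%, or below 25%. Maximum score: 100. Combinations: 3 × 3 = 9.

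**Step 1: both conditions required, or either one sufficient.** In the six off-diagonal cells, the first entry is the result if both are required and the second is the result if either suffices.

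| Symptom result | Gain >75% | Gain 25–75% | Gain <25% |
|---|---|---|---|
| Disappeared | obvious effect | none; obvious effect and improvement | none; obvious effect and invalid |
| Reduced | none; obvious effect and improvement | improvement | none; improvement and invalid |
| Not significantly improved | none; obvious effect and invalid | none; improvement and invalid | invalid |

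- Both required: 3 graded, 9 − 3 = 6 ungraded (6/9 = 67% of combinations).
- Either suffices: 0 ungraded, but the same 6 carry two grades.

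**Step 2: the most lenient reading.** Treat each threshold as a minimum, so that disappeared also counts as reduced and a gain above 75% also counts as at least 25%. Two more cells then become *improvement*: disappeared with 25–75%, and reduced with more than 75%. That leaves 6 − 2 = 4 ungraded: disappeared with <25%, reduced with <25%, and not improved with either of the two higher bands.

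**Step 3: a man without symptoms at baseline.** Only the bottom row of the table is open to him.

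- Both required, or thresholds as minimums: *invalid* if his gain is below 25%, no grade if it is 25% or more.
- Either suffices: with a gain of 25% or more he is graded favourably and *invalid* at once.

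On no reading does he receive a favourable grade alone.

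**Step 4: the ceiling of the scale.** Taking the percentages as relative to baseline *b*, the largest possible gain is (100 − *b*)/*b*.

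- A gain of 25% needs *b* ≤ 100/1.25 = 80.
- A gain above 75% needs *b* < 100/1.75 = 57.1.
- Examples: *b* = 60 allows at most 40/60 = 66.7%; *b* = 81 allows 19/81 = 23.5%; *b* = 90 allows 10/90 = 11.1%.

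A man who starts above 80 is always in the lowest band. If his symptoms disappear or lessen, he has no grade even on the lenient reading. For him the disagreement is forced by the scale. The Discussion makes high baselines plausible, since it speaks of "excluding patients who could not take care of themselves and had emotional cognition disorders", but the document gives no baseline ADL values.

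**The case against.** **The conditions are never joined by an explicit conjunction, so calling six combinations ungraded depends on the reading.** This stands, and it is why the point is worded as having no unique grade. Changing the reading moves the defect from no grade to two grades, or reduces it to four combinations; it does not remove it.

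**A condensed article may leave tie-breaking to the full protocol or an assessor manual.** This is fair for details that are left out. Here the rule is stated, and as stated it does not sort patients. A tie-break held elsewhere would settle the discordant cells, but it would also have to deal with men who have no symptoms at baseline.

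**The evaluator is blinded (section 2.6).** This stands as a limit on the harm: placement by judgement should mainly add noise rather than favour an arm. It does not supply the missing rule. Patients are not blinded, and symptoms such as nausea and numbness rest largely on what they report.

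Four stronger readings are tempting, and the document does not support them:

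- *That entrants have none of these symptoms.* Entry requires "The vital signs are stable and the stroke recovers", and the Discussion adds "patients had a recent stroke >3 months to ensure that the stroke was stable". The first may mean the recovery phase, and the symptom list is open-ended. Section 2.3 expects residual deficits in some men: "When the muscle strength returns to level 3, take active training".
- *That the grades cannot be applied at all to symptom-free men.* With a gain below 25%, such a man fits *invalid*. What he cannot reach is a favourable grade.
- *That two thirds of patients are affected.* Six of nine counts combinations, which are not equally likely. A head count would need the rate at which the two parts agree, and nothing in the document anchors one.
- *That the trial can say nothing about function.* The numeric score is collected before and after treatment, and section 2.7 gives methods for measurement data, although it does not tie one to this score by name.

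**Conclusion.** The point holds in this form. Six of nine combinations have no unique grade on the two direct readings, and four have none on the most lenient. With both conditions required, a man without symptoms at baseline is *invalid* or ungraded, whatever his functional gain. These results follow from the wording of section 2.4.2 and need no assumption about the patients. The ceiling figures assume that gains are relative to baseline; the count of combinations does not. The number of men affected is unknown.

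The graded secondary rate cannot be reproduced from the protocol as written and should be replaced before recruitment, which had not begun at submission. The primary IIEF-5 grades and the sample size do not depend on it.

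**What to change.** Settle first which instrument section 2.4.2 means: it names the NIH Stroke Scale but describes a 100-point daily-living scale. Once the daily-living scale is confirmed:

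1. Delete the symptom clause and the three composite grades.
2. Make the secondary outcome the total daily-living score at one named post-treatment visit, compared between arms with adjustment for the baseline score. The section says only that it is measured after treatment, and section 2.3 gives both a 2-week acupuncture course and an 8-week total. Week 8 is attached only to the IIEF-5, in the Abstract; the same visit would be a natural choice, but it has to be written down.
3. If symptoms are of interest, report them separately, among men who had them at baseline.

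The cost is small. The score is already planned before and after treatment, so the change is to the text, plus confirming the scale and the visit. The downside is losing the conventional graded efficacy table. Using the score does not remove the scale's ceiling, but it gives every assessed man a usable value.

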### Sample size calculation

2.5

According to the clinical experience, the effective rate of PSED in the intervention group was *P*1 = 0.80. The PSED effective rate of the control group was *P*2 = 0.50 (([two-sided type I error rate of 0.05, α = 0.05]; [one-sided type I error rate of 0.10, β = 0.10]). Substituting *f* (α, β) into the formula is as follows: n1 = n2 = 10.5 × (0.8 × 0.2 + 0.50 × 0.35) ÷ 0.152 = 48. The lost follow-up rate of patients will be controlled at 10%, so an additional 5 cases are added to each group. n1 = n2 = 53, that is, 53 cases will be taken from each of the intervention group and the control group. According to Cohen, this effect size is considered “moderate.”

### Randomization and blinding

2.6

Participants will be randomly allocated to the 2 groups through a sequence of numbers generated by a computer program before starting the selection process. The group assigned to each patient will be kept in a sealed envelope with the objective of concealing the assignment to the researcher, who will decide on the entry of subjects to the study. Given the nature of the interventions, the physiotherapists, and the patients, blinding will not be possible. However, the evaluator and statistician will be blinded to which group the subjects evaluated will belong.

### Statistical analysis

2.7

Data management uses EXCEL software to build a database, double entry, check for outstanding values, and lock. Statistical analysis will be performed using SPSS 25.0 software for statistical analysis. The normality of the measurement data is tested. The data obeying the normal distribution is Student's *t* test, which is expressed by mean ± standard deviation. The data not obeying the normal distribution is rank sum test. And marginal homogeneity test; count data are expressed by rate and composition ratio, and comparison is performed by chi-square test; repeated measurement data are expressed by mean ± standard deviation, intra-group comparison is performed by analysis of variance of repeated measurement data, and inter-group comparison is by multivariate analysis of variance (MANOVA). *P* ≤ .05 indicates that the difference is statistically significant.

### Data management

2.8

Information obtained from the evaluation of each participant will be recorded on a paper print-out. The information will then be handwritten on a paper document case report form and entered into an Excel file for future statistical analyses. In accordance with the Personal Information Protection Act, the names of all participants will not be disclosed, and a unique identifier number given during the trial will be used to identify participants. All of the participants will be informed that the clinical data obtained in the trial will be stored in a computer and will be handled with confidentiality. The participants’ written consent will be stored by the principal investigator.

